### Provisions for post-trial care

The experiment will be followed by a 6-month period with monthly telephone callbacks. At the same time, the trial was a low-risk intervention with no anticipated harm or compensation for participation.

### Statistical analysis

All statistical analyses were performed using SPSS v.27.0. Data are presented as means and standard deviations or proportions. Standard error of the mean (± SEM) was used to look at trends between cardiorespiratory and cerebrovascular changes during exercise and was more appropriate than SD, which was used to indicate the variability of data between patients. Statistical significance of differences between groups was assessed by analysis of variance, paired *t*-test and chi-square test. In addition, one-way ANOVA with repeated measures was used to determine statistically significant differences between the different percentiles of total exercise duration for oxy-Hb, Deoxy-Hb, Total-Hb, TSI, and blood oxygen saturation during exercise. Multiple comparisons using LSD honestly significant difference post hoc procedure to determine pairwise differences. Pearson’s correlation coefficient was used to assess the bivariate relationship. Multiple linear regression models were used to assess potential relationships between determinants of cognitive impairment and changes in cerebral oxygen utilisation and cerebral haemoglobin volume. Missing values in the data will be statistically analysed by multiple interpolation. The level of bivariate significance was set at *P* ≤ 0.05.

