## Research methodology

### Design

This study was a single-centre randomised controlled study with three measurement periods (One week before the experiment, week 6 of the experiment and the first week after the experiment.). Assessors for cognitive and physical tests and data analysts are formally blinded, while participants and trainers are unblinded. Eighty-one COPD patients (GOLD I-II) will be recruited for this study and randomly assigned in a 1:1:1 ratio to the HG, BDJ and CG groups, with the HG and BDJ groups receiving a 12-week motor rehabilitation intervention. The availability of oxygen in the dorsolateral prefrontal cortex (PFC) was monitored by fNIRS at all times during the cognitive task, and cognitive function was assessed in conjunction with relevant cognitive scales. To explore the improvement of cognitive function in COPD patients by strong abdominal breathing in a head-down position. This study design and participant flow is shown in Fig. 1, and the relevant demographic and baseline data indicators to be measured are shown in Table 1. For the study duration and SPIRIT checklist, please see the Additional file.

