For the measurement of the TSI, This study was designed to use a single-task walking test in two contexts. Also record the step frequency, step speed and walking time during the period. The first scenario was a single-task walk at a general pace (6 round trips on a 5-m trail analysis system for a total of 30 m). The general speed of the stride is based on the speed of walking at home. The second scenario is a fast walking single-task walk (6 round trips on a 5-m trail analysis system for a total of 30 m)[37, 38]. A fast walk is a guideline that mimics the speed of a fast walk through a junction. The status of altered cognitive function under the different intervention modalities was assessed by comparing oxygen saturation in the prefrontal cortex before and after the intervention, and by combining indicators such as step frequency, step speed and walking time during the period [39, 40]. In order to minimise experimenter-related methodological bias, the same assessor administered the same instructions to each subject. Each subject completed the task twice, once for familiarisation and once for assessment. Figure 4 shows the fNIRS instrument (portable NirSmart II-3000B Huitron Medical Devices Ltd.) that will be used in this study. It is possible to perform the relevant motor tasks in wireless transmission mode and record the cortical changes in oxyhaemoglobin during the performance of the task in continuous wave form. The light sources are fixed to the head cap at a distance of 30 mm, with a full channel sampling frequency of 11 Hz and wavelengths of 760 nm and 850 nm, respectively, with the detection area being the centre of each light detection point, and with specific brain area cues on the device to ensure accuracy of brain area monitoring.

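### A paired t-test is listed for differences between independent arms, and the listed analysis of variance has no stated baseline, change-score or group-by-time term

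*Protocol article*

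**What the plan says.** All references are to the protocol article.

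- **Design.** The trial is a "single-centre randomised controlled study with three measurement periods": one week before the experiment, week 6, and the first week after. Patients are "randomly assigned in a 1:1:1 ratio to the HG, BDJ and CG groups".
- **Statistical analysis, group tests.** "Statistical significance of differences between groups was assessed by analysis of variance, paired" *t*-test and chi-square test.
- **Statistical analysis, repeated measures.** In a separate sentence, introduced as an addition, "one-way ANOVA with repeated measures was used to determine statistically significant differences between the different percentiles of total exercise duration". TSI is one of the variables named there.
- **Statistical analysis, pairwise step.** "Multiple comparisons using LSD honestly significant difference post hoc procedure to determine pairwise differences".
- **Statistical analysis, regression.** Multiple linear regression relates determinants of cognitive impairment to changes in cerebral oxygen use. Arm is not mentioned.
- **Main results, TSI.** Altered cognitive function under the different interventions "was assessed by comparing oxygen saturation in the prefrontal cortex before and after the intervention", combined with gait measures.
- **Sample size.** ANOVA in G*Power, effect size 0.25, alpha 0.05, power 0.8, giving 69, raised to 81 for 10–15% attrition. The type of ANOVA is not named.

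**The concern.** A randomised comparison needs a test that sets one arm against another. A paired *t*-test uses two measurements on the same patient, so in this trial it can only ask whether one arm changed over time. Listing it for differences between groups is an error in the text, and a separate analysis plan would not make that sentence correct.

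The analysis of variance in the same sentence can compare the arms, but the section does not say whether it is applied to final values, change or a group-by-time term, or at which visit. The TSI section meanwhile describes a before/after comparison. A reader of the results could therefore be shown three within-arm tests and take a significant result in HG beside a non-significant one in CG as evidence of benefit. Any shift common to all arms, such as practice on repeated cognitive tests, can produce that pattern without a treatment effect. Precision is also at stake: a baseline value is collected, but no stated between-arm analysis uses it.

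**Working it through.** **1. Which listed analyses compare arms?**

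| Analysis named | Compares arms? | Uses baseline? |
|---|---|---|
| Analysis of variance | Can do so | Not stated |
| Paired *t*-test | No, within one arm | Yes, within the arm |
| Chi-square | Can, for proportions | Not stated |
| One-way repeated-measures ANOVA | No arm or visit factor; percentiles within exercise | No |
| Multiple linear regression | Arm not named | Concerns changes, not arms |

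**2. What test gives the stated 69?** Inputs from Sample size: f = 0.25 (read as Cohen's f), alpha 0.05, power 0.8. From Design: k = 3 arms, m = 3 visits. Power comes from the noncentral F distribution.

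- *Group-by-time interaction*, correlation ρ = 0, sphericity: λ = N f² m/(1 − ρ) = 69 × 0.0625 × 3 = 12.94, with df (k − 1)(m − 1) = 4 and (N − k)(m − 1) = 132. Power is 0.820. At N = 66 it is 0.799, so 69 is the smallest balanced total that reaches 0.80.
- *One-way ANOVA of three arms at one visit*: λ = N f² = 69 × 0.0625 = 4.31, df 2 and 66. Power is 0.43; at N = 81 it is 0.49. Reaching 0.80 takes N = 159.

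Of the one-way and repeated-measures variants tried, only the 3 × 3 interaction with ρ = 0 returned 69. The value ρ = 0 is not in the article; it is inferred from the match.

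**3. What would baseline adjustment give?** Assume that f = 0.25 is the effect on the unadjusted SD at one visit and that r is the baseline-to-follow-up correlation. The article gives no r; 0.5–0.7 is assumed. ANCOVA multiplies the error variance by 1 − r², so λ = N f²/(1 − r²), with df 2 and N − 4.

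| r | 1 − r² | λ at N = 69 | Power, N = 69 | Power, N = 81 |
|---|---|---|---|---|
| No adjustment | 1 | 4.31 | 0.43 | 0.49 |
| 0.5 | 0.75 | 5.75 | 0.54 | 0.62 |
| 0.6 | 0.64 | 6.74 | 0.62 | 0.69 |
| 0.7 | 0.51 | 8.46 | 0.72 | 0.80 |

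**4. What if within-arm tests were read as efficacy?** Assume no treatment effect, 69/3 = 23 patients per arm, and a shift of d SDs of change common to all arms. The paired test has noncentrality d√23 on 22 df and is significant with probability p. The arms are independent, so HG is significant and CG is not with probability p(1 − p).

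| d | p | p(1 − p) |
|---|---|---|
| 0.3 | 0.28 | 0.20 |
| 0.4 | 0.45 | 0.25 |
| 0.5 | 0.63 | 0.23 |

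A simulation with correlation 0.5 (SD of change then equals SD of the measurement) gave 19% at d = 0.3 and 23% at d = 0.5. The between-arm ANOVA stayed at 4–5% in the same simulated trials.

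**The case against.** A reader might infer that no stated analysis compares the arms. The article does not support that: analysis of variance comes first in the quoted sentence, chi-square is listed for proportions, and a pairwise procedure follows. An unadjusted ANOVA in a randomised trial is valid, and baseline adjustment improves its efficiency.

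A reader might also infer that baseline is ignored. It is not: the before/after comparison uses it within arms. It is absent only from the stated between-arm comparison. Nor is the repeated-measures ANOVA offered as a group test; lacking an arm factor is no defect in a within-session analysis. The point about it is narrower: it is the only place where TSI is named as a tested variable.

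The strongest over-reading is that the plan has a 20–25% false-positive rate. Nowhere does the article say that significance in HG without significance in CG will count as efficacy, and both the Introduction and the Discussion speak of comparing HG with BDJ. The figure describes a misreading that the wording permits. Its mechanism also fits the repeated cognitive scales better than TSI: selection on MMSE 23–27 does not by itself make TSI regress to the mean, and the walking task includes a familiarisation run.

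It can also be said that visit, covariates and model form are often left to an analysis plan, and that the match at 69 suggests a group-by-time analysis was intended. Both are fair and lower the severity. Neither corrects the misassigned paired test, and the second shows that the analysis section and the sample size have not been tied together.

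**Conclusion.** The point holds in a limited form, as something that should be fixed. The firm part needs no assumption: a paired test is assigned to a comparison of independent arms, and no baseline, change or group-by-time term is stated for the analysis of variance that could make that comparison.

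The sizes are conditional. The gain from 43% to 54–72% power at 69 patients assumes f = 0.25 at a single visit and correlations of 0.5–0.7. It is not a statement about the power of the article's own design, because f = 0.25 in an interaction test is a different quantity. The 20–25% assumes a common shift of 0.3–0.5 SD of change and a decision rule that the article does not contain.

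**What to change.** In Statistical analysis:

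1. Remove the paired *t*-test from the tests of group differences. Keep it, if wanted, as within-arm description with no efficacy claim.
2. State the between-arm analysis of TSI: ANCOVA of the value in the first week after the intervention on arm and baseline value; or a mixed model over week 6 and post-intervention with arm, visit, arm-by-visit and baseline. Report the HG–CG and HG–BDJ differences with 95% confidence intervals.
3. Use the same model for the continuous secondary outcomes.
4. Label the exercise-percentile ANOVA exploratory.

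In Sample size, name the test and the correlation behind 69, and restate power for the model chosen in item 2.

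The cost is wording and a short recalculation. SPSS 27 fits both models and all the measurements are already scheduled. Since Trial status expects completion by April 2024, the change should be dated and recorded before anyone analyses the data by arm.

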## Discussion

This study will examine the improvement of cognitive function in patients with COPD combined with MCI in terms of physiological indicators and assessment scales. In the past, patients with cognitive impairment have been excluded from PR programmes for COPD patients due to their frequent memory loss, dysfunction, and poor physical and mental health, which hinder the effectiveness of PR interventions [8]. There is a need to explore treatments that can improve cognitive function in COPD patients in order to improve the quality of their survival [41]. Aras et al. [42] showed that the coexistence of sleep disturbance, depression and anxiety with COPD increased cognitive impairment and the severity of the disease. In a study on the relationship between cognitive function and the brain, Savage et al. [43] found in their study that frontal lobe atrophy was significantly greater in COPD patients than in controls (*p* = 0.02) using a visual rating scale, and that cognitive function was significantly worse in the COPD group in terms of executive function (*p* < 0.001), working memory (*p* = 0.02), verbal memory (*p* = 0.03) and processing speed (*p* = 0.001) were significantly worse. In a PR programme for a population of patients with COPD combined with cognitive impairment, Andrianopoulos et al. [44] compared cerebral oxygen availability during exercise in cognitively impaired (CI) and cognitively normal (CN) COPD patients. During exercise, CN and CI patients exhibited mild to moderate decreases in SpO2 (nadir [Δ] ≥  − 3 ± 2% and – 5 ± 3%, respectively) but maintained baseline frontal cortical TSI levels, while presenting small TcPCO2 perturbations and increased total brain-Hb (post [Δ] ≥ 2.0 ± 3 μM s − 1). Patients with CI retain the ability to adequately maintain cerebral oxygen availability during submaximal exercise. Therefore, rehabilitative exercise training for patients with COPD combined with CI who exhibit mild to moderate exercise-induced decreases in SpO2 does not appear to result in reduced cerebral oxygen availability. As in healthy older adults, cardiorespiratory fitness is positively associated with cognitive function in COPD patients [45], and cognitive function in COPD patients can be improved by targeted cardiorespiratory interventions in PR programmes.

Ba Duan Jin is a traditional Chinese sport with a long history, easy to learn and highly effective. The practice of Ba Duan Jin requires no equipment, is not limited by space, and has significant effects on strengthening the body, regulating the movement of qi and blood in the internal organs, and improving respiratory function [46]. Yang et al. [47] concluded from a study of patients with mild COPD that traditional Ba Duan Jin exercises can prevent the deterioration of lung function in COPD and provide a simple, inexpensive, and routine pulmonary rehabilitation measure for patients with mild COPD. This experiment compares the Baduanjin group with the HG group, thus arguing for the effectiveness of the HG training method to be significant.

Strong abdominal breathing, as a form of breathing, intervenes on the respiratory muscles as well as on the carotid blood flow by means of postural adjustments and the diaphragm. In previous studies, head-down training has been found to have a rehabilitative effect in the musculoskeletal system [48], and Su Quansheng et al. [49] showed increased myocardial excitability and improved myocardial contractile performance in the prone and inverted positions in humans. Guo et al. [18] showed that changes in carotid blood flow were related to body position and also had a further contribution to the reduction of psychological stress and improved sleep quality in the lives of older people. However, Guo et al. [50] also studied the head-down bed rest manoeuvre and found that human lung function was not affected. It has also been shown that regular and quantitative inversion training improved the central nervous function of archers and significantly alleviated adverse emotions such as anxiety, poor sleep quality and other discomfort symptoms in good archers after load training [51, 52]. Regarding the control of the angle of the head-down position and respiratory rate, we referred to the angle (0–90°) and respiratory rate (35 breaths/min) of the head-down position performed in the previous period in healthy university students as well as in the elderly. It also combined the characteristics of COPD patients in terms of cardiorespiratory function, etc., the angle of head-down position was proposed to be adjusted to − 30°, and the respiratory rate was proposed to be adjusted to 25 breaths/min. The head-down angle and respiratory rate will also be assessed before the formal experiment, and the angle will be adjusted according to the patient’s actual condition.

For the improvement of cognitive function in patients with COPD combined with MCI, We analysed data on the status of changes in oxyhaemoglobin in the prefrontal cortex of the brain during the task (walking) as detected by fNIRS. The fNIRS analysis only considered the single-task condition, as we expected confounding behavioural differences to occur in the dual-task condition, and therefore the fNIRS analysis was not valid in this condition [53]. However, fNIRS will inevitably generate noise and artefacts during the motion task [54–56], such as breathing, heartbeat, environmental noise and instrument noise, which will interfere with the reliability of the experimental data analysis [57], We will also correct the relevant data. However, in order to enhance the true reliability of the experimental results, we will also assess cognitive functioning more comprehensively with the internationally used Montreal Cognitive Assessment Scale (MoCA), the Revised Addenbrooke’s Cognitive Examination (2012) ACE-R and specific cognitive domains (i.e. attention (Attention Matrix Test), memory (Digital Breadth Test DST), executive ability (TMT Connectedness Test A-B), fluency (VFT)) and cognitive behavioural ability level tests.

In conclusion, this study will explore a new community-based PR programme for patients with COPD combined with IC in order to promote its application in the general population. The HG will be used to intervene in the cognitive function, mental status and motor ability of patients with COPD combined with MCI, and to select a proven intervention that will enrich the current PR programme for COPD.

### Strengths of this study

According to currently available information, the HG breathing training method is not found in the PR programme for COPD, and the inverted and upside-down exercise equipment used in this study is a nationally recognised and patented product, whose design and use have been recognised by many. The research project leader is one of the patent holders of the product and has also participated in HG-related research, which will provide more professional guidance and support for this study.This study combines conventional cognitive measurement scales and fNIRS to make the experimental findings more objective and scientific by combining quantitative physiological and biochemical indicators with cognitive assessment.We will explore PR programmes for COPD in the community, where HG training apparatus and equipment are relatively inexpensive and easy to implement for home and community-based organisations.

### Shortcomings of this study

Patients need to actively cooperate with each breathing exercise during the performance of head-down strong abdominal breathing, but the implementation process does not allow for precise detection of the patient's breathing pattern, which requires us to enhance the ideological education of the subject prior to the intervention.The assessment results may be influenced by the subjective bias of this researcher, as the blinded intervention was not performed during the administration to the subjects.

## Trial status

Participants will take place from 1 January 2024 to 31 January 2024. This study is expected to be completed by April 2024. This study protocol has been submitted prior to the end of recruitment and prior to the last patient. This study has been registered with the Chinese Clinical Trial Registry on 4 September 2023 (https://www.chictr.org.cn/).

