### Recruitment and selection

This study will rely on COPD patients associated with the respiratory department of Anqing Hospital of the People’s Liberation Army Navy and COPD combined with CI patients in the surrounding community of this hospital for sample recruitment to ensure adequate sample size, ease of implementation of the relevant experimental protocol and to reduce sample attrition. Recruitment for This study in this experiment will take place on 1 January 2024, and on 1 February 2024, the 12-week experimental period will officially begin. Relevant medical data and screening will be evaluated by a medical professional. Subjects will also sign an informed consent form indicating their voluntary participation in the trial. The protocol follows the Standard Protocol Items: Recommendations for Interventional Trials (SPIRIT) 2013 [27]. A brief SPIRIT flow diagram is shown in Table 2. A populated SPIRIT checklist is provided in the Additional file.

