### Intervention

#### Head-down strong abdominal breathing group (HG)

Patients will have a week before the experiment to focus on understanding and learning the head-down strong abdominal exercise to ensure that the participants in the group can perform the relevant movements in a standard way during the formal experiment. During the experiment, head-down strong abdominal breathing will be performed in accordance with the experimental requirements, from easy to difficult, and the participant will be asked to empty their bowels and to perform the head-down strong abdominal breathing at least 1 h after a meal, and to complete the training in one session. The intensity of the intervention was 40 min three times per week, including 5 min of warm-up and acclimatisation at the beginning of the exercise, 30 min of head-down strong abdominal breathing, 5 min of stretching and relaxation, with a respiratory rate of 25 breaths/min (metronome cue), and head-down training on an inverted upside-down dual-purpose exercise machine (Patent No. 201821510570.5) at an inclination angle of − 30°. The intervention period was 12 weeks. Figure 2 shows the field pictures of the carotid blood flow characteristics and the factors influencing it in different positions in young people studied by the head-down strong abdominal breathing in the early stage of this research project [28].This study will also use this inverted upside-down dual-purpose exercise machine to perform head-down strong abdominal breathing exercises.

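### Recruitment open to 31 January with a common start on 1 February leaves patients recruited on 25–31 January without the full baseline and learning week that the protocol describes

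*Protocol article*

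**What the plan says.** All references are to the protocol article.

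- **Recruitment window** (Trial status): "Participants will take place from 1 January 2024 to 31 January 2024".
- **Common start** (Recruitment and selection): "on 1 February 2024, the 12-week experimental period will officially begin".
- **Assessments** (Design): there are three, at "One week before the experiment, week 6 of the experiment and the first week after the experiment".
- **HG preparation** (Intervention, HG): "Patients will have a week before the experiment to focus on understanding and learning the head-down strong abdominal exercise". The stated purpose is that participants in that group perform the movements correctly once the formal experiment starts. The Discussion adds that head-down angle and respiratory rate are also assessed before the formal experiment.
- **Other arms** (Intervention, BDJ and CG): no learning week is described for the Ba Duan Jin group, and the control group has no systematic exercise.
- **End** (Trial status): "This study is expected to be completed by April 2024".

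**The concern.** The dates for recruitment and start appear in two sections, and the preparation that must fit between them appears in two others. Together they do not fit for everyone. The last recruitment day is the day before the start, yet a baseline assessment and, for HG, a week of learning must both come before the start.

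Two things are at stake. First, late HG recruits would begin with less training than the plan relies on. That matters because the protocol concedes, under Shortcomings, that breathing pattern cannot be precisely checked during sessions and that preparation beforehand has to make up for it.

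Second, the learning week is for members of the HG arm and so comes after allocation. If baseline is taken in the same days, some HG patients may have the prefrontal oxygenation index (the main outcome) and the cognitive tests measured after they have begun to practise. Control patients have no such practice, and none is described for BDJ. The baseline would then not mean the same thing in each arm, and the before-and-after comparison rests on it.

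**Working it through.** **Inputs.** Recruitment 1–31 January 2024 (Trial status). Start 1 February 2024 and length 12 weeks = 84 days (Recruitment and selection). Baseline and HG learning each in the week before the start (Design; Intervention, HG). Post-test in the first week after (Design). 2024 is a leap year.

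**Step 1: the plan's own completion date.**
- Last treatment day = 1 February + 83 days = 24 April.
- Post-test week = 1 February + 84 to + 90 days = 25 April to 1 May.
- Six of the seven post-test days fall in April, so the stated completion reproduces to within one day.

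**Step 2: the preparation week.**
- Start − 7 to start − 1 = 25 to 31 January.
- These are the last 7 of the 31 recruitment days: 7/31 = 23%.

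**Step 3: who has a full week.** Count full days after the day of recruitment and before 1 February, that is 31 minus the January date.

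| Recruited on | Full days left | Baseline and learning in parallel (7 needed) | In sequence (14 needed) |
|---|---|---|---|
| 17 January | 14 | fits | fits |
| 24 January | 7 | fits | does not fit |
| 25 January | 6 | does not fit | does not fit |
| 31 January | 0 | does not fit | does not fit |

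Counting the recruitment day itself moves each limit by one day and changes nothing else.

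**Step 4: how many patients.** The document gives no accrual pattern, so the number is unknown. If, as an assumption, the 81 patients arrived evenly over January:
- Parallel: 81 × 7/31 = 18.3 patients, or about 6 per arm (18.3/3 = 6.1).
- In sequence: days 18–31 are 14 of 31, so 81 × 14/31 = 36.6 patients, or about 12 per arm.

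Early accrual would bring the parallel figure towards zero, and late accrual would raise it.

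**Step 5: dates that would fit with recruitment to 31 January.**
- Parallel: preparation 1–7 February, start 8 February, last treatment day 1 May, post-test 2–8 May.
- In sequence: preparation 1–14 February, start 15 February, last treatment day 8 May, post-test 9–15 May.

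**The case against.** The strongest reply is that this is a small mismatch of dates. Anyone recruited by 24 January, 24 of the 31 days, fits if baseline and learning share the week, and nothing in the text forbids that. The recruiters may have filled the trial early. Sample size and significance level are untouched. All of this stands, and it limits the point to late recruits and to the order of baseline and HG practice. It does not remove the conflict, because recruitment is expressly open to 31 January. Sharing the week is also what allows practice to precede the HG baseline.

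A reader might infer more, and the document does not support it:

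- **That April completion is badly wrong.** The overrun is one day. The later calls ("The experiment will be followed by a 6-month period with monthly telephone callbacks") stand under post-trial care with no outcome attached, so they contradict the April date only if counted as part of the study.
- **That one assessor must test 81 patients in a week.** The sentence "the same assessor administered the same instructions to each subject" concerns the walking task. Elsewhere the article speaks of assessors in the plural and has clinicians measure lung function. The document gives no duration for the test battery.
- **That patients who exacerbate in January enter unchecked.** The exclusion criteria give a 4-week window without a reference date, and the schedule table is not shown. The absence of a recheck would be an inference from silence. The article makes no seasonal argument either.
- **That baseline would be taken after treatment starts.** No section allows this.

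**Conclusion.** The point holds in a limited form. Recruitment to 31 January with a common start on 1 February contradicts the baseline week in the Design section and the learning week in the HG section for patients recruited on 25–31 January (7 of 31 days, 23%). It also leaves HG baseline testing open to overlap with practice that the control group does not have.

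This assumes that the preparation week means seven full days after recruitment and that the 1 February start is common to all patients, as the text reads. The number affected is unknown; about 18 of 81 follows only from assuming even accrual. The effect on the main outcome cannot be sized. If early practice acts in the same direction as the 12-week programme, HG change would be understated.

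The issue concerns the timing and comparability of baseline. It does not concern power or error rate, and the calendar is workable for patients recruited earlier.

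**What to change.** Reconcile Trial status and Recruitment and selection with Design and the HG section in one of these ways:

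1. **Preferred:** count baseline, learning week, week 6 and post-test from each patient's own start. State that baseline is completed before allocation and before any HG practice.
2. **Simpler:** keep 1 February and close recruitment by 24 January (17 January if baseline and learning run in sequence).
3. **Simpler:** keep recruitment to 31 January and move the common start to 8 February or later (15 February if in sequence).

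Under options 2 and 3 with the two activities in parallel, the order within the week still has to be stated: baseline first, then allocation and practice.

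Restate expected completion as the last post-test: 1 May 2024 on the present calendar, or about 8–15 May if the start moves. As a minor query, ask that the exclusion criteria and the recruitment section state the date to which the 4-week exacerbation window refers.

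The cost is a slightly longer calendar, a protocol amendment and a registry date update. Option 1 also spreads supervised sessions over a longer period.

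The article is dated 30 May 2024, after all of these dates. If the trial ran to this calendar, the remaining step is to report each patient's dates of recruitment, allocation, baseline and first practice. The main comparison could then be repeated without patients recruited on 25–31 January, in all three arms alike.
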